## Abstract

**Background:**

Vitamin D deficiency is common in patients with end stage kidney disease (ESKD) and is a strong predictor of death from cardiovascular disease, infections and cancer. Currently only 68% of patients in the UK survive 3 years or more on dialysis. Vitamin D replacement typically utilises activated (1α-hydroxylated) vitamin D compounds allowing for impaired renal activation. However, this approach increases blood calcium concentrations and may paradoxically accelerate vitamin D catabolism. Contemporary treatment guidelines recommend replacement with inactive (unhydroxylated) vitamin D_3_ (cholecalciferol), instead relying on autocrine and paracrine vitamin D activation in target tissues. However, the impact of this approach on clinical outcomes has not yet been tested in adequately powered trials.

**Methods:**

The SIMPLIFIED (Survival Improvement with Cholecalciferol in Patients on Dialysis) trial will test whether supplementation with high-dose cholecalciferol improves survival. Adult dialysis patients will be recruited from one of 72 UK renal centres, by local clinicians and research nurses, and randomly assigned in a 1:1 ratio to high-dose open-label cholecalciferol or standard care, stratified by site. Trial outcomes will be captured using existing data sources including Office of National Statistics (ONS) for deaths and Hospital Episode Statistics (HES) for secondary endpoints. The primary endpoint of the trial is all-cause mortality. Key secondary endpoints include survival free from cardiovascular events, infections and cancers, and quality of life and cost-effectiveness measures utilising the Eq5D tool. Severe adverse event line listings will be generated from HES data for safety reporting. In this superiority trial, it is anticipated that approximately 4200 patients in total will need to be enrolled to observe 2200 deaths over a period of about 7 years, which will yield 90% power to demonstrate a hazard ratio of 0.87.

**Discussion:**

Outcomes for patients on dialysis remain very poor. The pragmatic design of this study leveraging routinely collected data streamlines trial conduct, reducing burden on patients and local site study staff. Furthermore, since cholecalciferol is a low-cost and easy to administer intervention, evidence of benefit could be readily incorporated into dialysis care across healthcare systems globally.

**Trial registration:**

EudraCT Number: 2015-005003-88; ISRCTN Number: 15087616 (registration date 30th December 2015) (https://doi.org/10.1186/ISRCTN15087616). Recruitment commenced in March 2017.

## Administrative information

Note: the numbers in curly brackets in this protocol refer to SPIRIT checklist item numbers. The order of the items has been modified to group similar items (see http://www.equator-network.org/reporting-guidelines/spirit-2013-statement-defining-standard-protocol-items-for-clinical-trials/).

## Introduction

### Background and rationale {6a}

In the United Kingdom (UK), nearly 30,000 people receive regular dialysis, and 6000 new patients start dialysis each year. Although this is a life-saving treatment, dialysis-requiring kidney failure carries a worse prognosis than most malignancies [1], with a mean 3-year survival of only 68%. The mean age of UK dialysis recipients is 65 years, and after 4 years on dialysis, fewer than 40% of those aged 65 and over survive. Those aged 60–69 years have nine times the relative risk of death compared to the UK general population. The three leading causes of death are cardiovascular disease, infections and malignancy [1]. Patients receiving maintenance dialysis experience significant physical, emotional, mental and psychological impairments which are reflected in health-related quality of life (HRQoL) scores [2].

Treatment of patients with end stage kidney disease (ESKD) is disproportionately costly, accounting for up to 2% of the National Health Service (NHS) healthcare budget whilst representing only 0.05% of the population [3]. Despite this, nephrology has historically lagged behind most disciplines in testing interventions in randomised trials [4]. A key obstacle to trials in dialysis is the readiness with which treatment guidelines are accepted into clinical practice without adequate prior evaluation or introduction in a randomised manner. A wide range of interventions currently employed in this population in the NHS, at considerable cost, are aimed at improving survival and quality of life, but have either failed to show any benefit (erythropoiesis-stimulating agents [5], lipid-lowering agents [6], calcimimetics [7]) or have not been adequately evaluated in randomised trials (phosphate-lowering agents or active vitamin D compounds).

In patients with kidney disease, plasma 25(OH)D, the main circulating form of vitamin D, begins to decline when the glomerular filtration rate falls below 45 ml/min/1.73 m^2^. Once patients reach dialysis, only a small minority are vitamin D sufficient. In a cohort of 6518 German dialysis patients, 76% were vitamin D deficient [8]. Despite the introduction of national and international guidelines recommending the measurement and supplementation of vitamin D in patients on dialysis, reports over the past decade consistently show vitamin D deficiency in this population [9–11]. Dialysis patients are typically treated with active 1α-hydroxylated vitamin D compounds, such as alfacalcidol or paricalcitol, a practice inherited from the now disproven belief that activation through 1α-hydroxylation occurred only in the kidneys. It is now known that synthetic and catabolic hydroxylases are ubiquitously expressed and the vitamin D endocrine system is involved in a wide range of cellular functions including cellular growth, proliferation, apoptosis and inflammation [12]. Whilst the use of 1α-hydroxylated compounds is effective in lowering parathyroid hormone levels, their use is associated with hypercalcaemia, worsening hyperphosphataemia, potential acceleration of vascular calcification and potent induction of vitamin D catabolism, thus potentially worsening systemic and cellular vitamin D deficiency. In contrast, the administration of cholecalciferol would circumvent all of these limitations and is both low-cost and readily available.

A large body of epidemiological evidence supports a role for vitamin D in reducing cardiovascular disease, malignancy and infections. In otherwise healthy persons, deficiency is strongly associated with cardiovascular, cancer and all-cause mortality, and key pathways in host defence are dependent upon vitamin D sufficiency [13]; each 25 nmol/L reduction in 25(OH)D was associated with a 16% increase in all-cause mortality in a large meta-analysis including data from 849,412 subjects. The pooled relative risk (RR) was 1.35 (95% CI 1.13 to 1.61) for death from cardiovascular disease, 1.14 (1.01 to 1.29) for death from cancer, 1.30 (1.07 to 1.59) for non-vascular, non-cancer death and 1.35 (1.22 to 1.49) for all-cause mortality [14].

However, two large trials with over 30,000 participants have not shown significant benefit of vitamin D supplementation in patients without chronic kidney disease (CKD) [15, 16]. The VIDA (Vitamin D Assessment) study did not demonstrate any significant reduction in incident cardiovascular disease or death in those treated with cholecalciferol versus placebo (adjusted hazard ratio, 1.02; 95% CI, 0.87–1.20) [15]. The VITAL study demonstrated that vitamin D did not lower the incidence of major cardiovascular events (HR 0.97; 95% CI, 0.85–1.12) or cancer incidence (HR 0.96; 95% CI, 0.88–1.06) [17]. However in patients with kidney failure, one small trial of 126 patients randomised to high-dose ergocalciferol or placebo demonstrated reduced cardiovascular events in the ergocalciferol arm (HR 0.37, 95% CI 0.14–1.0) [17].

The Kidney Disease Improving Global Outcomes (KDIGO) initiative accept that current evidence is lacking and identifies vitamin D supplementation in dialysis as a key research objective, but nevertheless argues for its use on the basis that the intervention is safe and inexpensive [18]. Caution is necessary, however, when extrapolating from epidemiological data. Observational data similarly supported the use of antioxidant vitamins including vitamins C and E, which were found to be of no benefit or even harmful in adequately powered interventional trials [19, 20]. Widespread supplementation with cholecalciferol should therefore be rigorously tested in an adequately powered randomised trial prior to implementation.

At conception of this trial, a survey of UK renal units illustrated that vitamin D was neither routinely measured nor supplemented in the UK dialysis population. In contrast to other countries where supplementation is already more prevalent, this lag in implementing existing guidelines provides the opportunity to test the hypothesis that cholecalciferol improves survival and quality of life in a population that is mostly treatment naïve. The SIMPLIFIED trial will address this clear unmet need for an adequately powered clinical trial to assess the impact of cholecalciferol on quality of life and survival in ESKD before evidence–poor guideline-driven vitamin D replacement becomes entrenched in clinical practice.

### Objectives {7}

#### Primary objective

To determine the effect of cholecalciferol (60,000 IU fortnightly) on patient survival.

#### Secondary objectives

To determine the effect of cholecalciferol (60,000 IU fortnightly) on hospital admissions due to cardiovascular events, infections or fracture, cancer incidence, quality of life and evaluate the cost-effectiveness of cholecalciferol from the perspective of the NHS.

### Trial design {8}

SIMPLIFIED is a prospective, randomised, open-label, pragmatic, multi-centre registry-facilitated superiority trial of cholecalciferol (also known as colecalciferol) versus standard care in patients receiving dialysis.

## Methods: participants, interventions and outcomes

### Study setting {9}

There are 72 renal units across the UK that contribute data to the UK Renal Registry (UKRR). It is anticipated that the SIMPLIFIED trial will be conducted in up to 65 of these units.

### Eligibility criteria {10}

#### Inclusion criteria

To be included in the trial the patient must:Have given written informed consent to participateBe aged 18 years or overA UK residentHas ESKD requiring dialysis

#### Exclusion criteria

The presence of any of the following will preclude patient inclusion:Treatment with high-dose (> 1000 IU/day) cholecalciferol or ergocalciferol in the last 30 daysPersistent hypercalcaemia (corrected calcium > 2.62 mmol/l on three separate and sequential occasions without precipitating cause)Hypersensitivity to cholecalciferol or any of the excipients of the productLife expectancy < 6 monthsWomen who are pregnant/planning to become pregnant or are breastfeedingOpted out from contributing data to the UK Renal Registry (UKRR)

### Who will take informed consent? {26a}

Consent will be obtained by the principal investigator (PI) or by a suitably qualified and delegated health professional and member of the research team at each site. The patient will be provided with the approved Patient Information Sheet at a routine dialysis appointment. If the patient is interested in the study, a member of the study team will discuss the study with them and answer any questions they may have, usually at a subsequent dialysis appointment but trial discussions could also take place by telephone. The investigator or designee will obtain written, informed consent from each patient before any study procedures are undertaken.

In specific cases, such as when access to dialysis units is restricted or patients receive home dialysis, consent can be taken remotely via telephone or other audio/visual teleconference methods by the PI or a delegated team member. If remote consent is obtained, then the copy of the Informed Consent Form sent to the patient via post is signed by the participant and then sent back for signature by the PI or delegated team member who took the consent remotely as soon as it is received. Face to face consent will still be the primary method of consent and this remote method should only be used when face to face is not possible.

### Additional consent provisions for collection and use of participant data and biological specimens {26b}

Trial participants will provide explicit consent for the collection and use of patient identifiable data (name, date of birth, gender, NHS number or equivalent, home address and postcode, telephone number and/or email address) for the purposes of the conduct of the trial. Patient identifiable data will be stored separately from anonymised trial data on a secure server hosted within University of Cambridge. This data is required for linkage with routinely collected datasets obtained via NHS England and devolved nation equivalents to gather data on primary and secondary endpoints, deaths and hospital admissions respectively, and is therefore imperative for the conduct of the trial.

## Interventions

### Explanation for the choice of comparators {6b}

Participants randomised to the control group will receive standard care based on local treatment guidelines but will not be permitted to receive cholecalciferol or ergocalciferol > 1000 IU per day for the duration of the study, unless vitamin D deficiency-related osteomalacia is diagnosed.

### Intervention description {11a}

Patients randomised to receive cholecalciferol will be prescribed cholecalciferol 60,000 IU fortnightly, in addition to standard care. Where their standard care already involves the administration of low-dose cholecalciferol or ergocalciferol (≤ 1000 IU/day), the relevant prescription must be discontinued upon randomisation to the cholecalciferol group and prior to the administration of the first trial dose.

### Criteria for discontinuing or modifying allocated interventions {11b}

Circumstances may arise under which cholecalciferol will be temporarily discontinued or dose reduced for participants in the interventional arm. Discontinuation of trial drug does not constitute withdrawal from the trial. Discontinuation may occur under the following circumstances:Vitamin D toxicity. Hypercalcaemia (Fig. 1) and vitamin D toxicity (Fig. 2) algorithms are illustrated below, and cholecalciferol may be discontinued if there is persistent toxicity despite prior institution of the dose change recommendations.Severe adverse reactions (SAR or SUSAR) or adverse reactions which in the opinion of the PI requires discontinuation of cholecalciferol.

**Fig. 1 Fig1:**
[figure not shown]
Hypercalcaemia algorithm. Ca, calcium; P, phosphate. Given that cholecalciferol treatment should at least partially restore endogenous calcitriol synthesis, the reduction or withdrawal of active vitamin D compounds should be prioritised. *Active vitamin D: all 1α-hydroxylated vitamin D compounds including (but not limited to) alfacalcidol, paricalcitol, calcitriol and 22-oxacalcitriol

**Fig. 2 Fig2:**
[figure not shown]
Suspected vitamin D toxicity. If all identifiable causes of hypercalcaemia (Fig. 1) have been excluded or addressed, vitamin D toxicity should be considered in patients receiving cholecalciferol. This includes discontinuation of 1α-hydroxylated vitamin D compounds, since toxicity results from increased circulating calcitriol concentrations. Therefore, vitamin D toxicity cannot be attributed to cholecalciferol in the presence of concomitant treatment with 1α-hydroxylated compounds

Participants may withdraw consent for continuation in the trial at any point. Withdrawal will constitute discontinuation of the trial drug for those in the cholecalciferol arm. In the event that a participant withdraws from the trial, ongoing data capture through linkage will continue unless the participant also withdraws from data linkage and any future data capture.

Trial participants who receive a kidney transplant or become pregnant should be withdrawn from cholecalciferol if in that group; however, they will remain within the trial providing ongoing data captured through linkage unless the participant withdraws from data linkage.

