### Adverse event reporting and harms {22}

This trial is categorised by the Medicines and Healthcare products Regulatory Agency as a type A study (no higher than the risk of standard medical care). Patients are followed up regularly at their local dialysis units throughout this study, and an ongoing evaluation of risk will continue throughout the recruitment period.

Serious adverse events (SAEs) will not be recorded and reported within the usual 24-h time period but will instead be captured using the routine data sources. SAE line listings will be periodically generated and reviewed by the chief investigator and reported to the sponsor. Serious adverse reactions or suspected unexpected reactions that are directly attributable to cholecalciferol will require reporting by site teams to the SIMPLIFIED trial office within 24 h of awareness.

Dialysis patients are intensively monitored as part of standard care with comprehensive biochemical and haematological tests being performed at least monthly. All dialysis data for each patient are reviewed by renal unit staff, typically in “sit down ward round” meetings, where clinical parameters and test results are reviewed and treatments adjusted. This approach will allow rapid detection of elevated calcium levels which is a potential concern with the administration of high-dose cholecalciferol, and clear guidance is provided to sites should hypercalcaemia occur via the hypercalcaemia (Fig. 1) and vitamin D toxicity (Fig. 2) algorithms.

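### As worded, the Fig. 2 legend and the direct-attribution trigger let a serious toxicity case on both drugs go without a 24-hour site report

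*Protocol article*

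**What the plan says.** Three parts of the protocol article bear on this point.

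- **Criteria for discontinuing or modifying allocated interventions {11b}, Fig. 2 legend.** The entry condition is "If all identifiable causes of hypercalcaemia (Fig. 1) have been excluded or addressed, vitamin D toxicity should be considered in patients receiving cholecalciferol". The legend counts stopping 1α-hydroxylated compounds among the steps to take first, because "toxicity results from increased circulating calcitriol concentrations". It then concludes that "vitamin D toxicity cannot be attributed to cholecalciferol in the presence of concomitant treatment with 1α-hydroxylated compounds". The Fig. 1 legend gives the reason for cutting active vitamin D first: "cholecalciferol treatment should at least partially restore endogenous calcitriol synthesis".
- **Adverse event reporting and harms {22}.** "Serious adverse events (SAEs) will not be recorded and reported within the usual 24-h time period"; they come from routine data instead, and "SAE line listings will be periodically generated and reviewed by the chief investigator and reported to the sponsor". The 24-hour site route is reserved: "Serious adverse reactions or suspected unexpected reactions that are directly attributable to cholecalciferol will require reporting" within that time. A later paragraph of the same section, on routine blood-test review, says that "clear guidance is provided to sites should hypercalcaemia occur via the hypercalcaemia (Fig. 1) and vitamin D toxicity (Fig. 2) algorithms".
- **Relevant concomitant care {11d}.** Every patient may stay on active vitamin D. The article expects the need for it to fall under cholecalciferol and asks for regular review of those prescriptions. Background and rationale {6a} describes active compounds as the typical treatment in dialysis.

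**The concern.** The legend makes a statement about causality, without qualification, inside an algorithm that sites are told to follow. The reporting rule turns on causality. A site that takes both literally has a written reason not to send a 24-hour report on a serious toxicity case if the patient is also taking alfacalcidol, paricalcitol or a similar drug.

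At stake is the speed of one safety route. SAEs are outside 24-hour reporting by design, so the site report of a serious or unexpected reaction is the only 24-hour route the article describes. Raised calcium is the harm that the article itself names as a potential concern with high-dose cholecalciferol. Co-treatment with active vitamin D is the usual starting position, so the legend's condition would not be rare early in follow-up. The point covers vitamin D toxicity only, not all hypercalcaemia, and it does not touch the primary endpoint or its analysis.

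**Working it through.** The plan gives no figure to reproduce on this point. The check sets the statements side by side.

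**Step 1: do the premises support the legend's conclusion?**

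- Premise A (Fig. 2 legend): toxicity comes from raised circulating calcitriol.
- Premise B (Fig. 1 legend): cholecalciferol restores at least part of the body's own calcitriol production.
- Added fact: the legends treat active vitamin D as a competing source, to be cut first.

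A patient on both drugs therefore has two possible contributors to one event. What follows is that the event cannot be attributed to cholecalciferol alone, or that the two contributions cannot yet be separated. The legend's conclusion omits that qualifier, so it goes beyond its premises.

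**Step 2: what does the reporting rule do with each reading of the legend?** Take a serious toxicity case in a patient still on both drugs at the moment the site becomes aware of it.

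| Reading of the legend | Status at awareness | Passes the direct-attribution test in {22}? |
|---|---|---|
| Cholecalciferol is not the cause | Not attributable | No |
| Cause cannot be assigned until active vitamin D is stopped | Not yet attributable | Not yet |

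On either reading the site may hold back the 24-hour report. On the second, attribution becomes possible only once the active compound has been stopped, and the clock runs from awareness. The rule is also strained internally: it joins suspected reactions, a low threshold, to direct attribution, a high one.

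**Step 3: does other text rescue the case?** The clause in {11b} that relies on the principal investigator's opinion governs stopping the drug, not reporting. Three other sources do not depend on site attribution:

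- the periodic line listings {22}, which the Abstract says are generated from HES;
- UK Renal Registry calcium, under Participant timeline {13} and the laboratory section {33};
- unblinded IDMC review {21a}.

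A case can surface through any of these, but the article ties none of them to a 24-hour clock. It also does not say whether the listing review includes a causality judgement.

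**Step 4: size.** The number of reports not expedited would be the number of patients in the cholecalciferol arm, times the share on active vitamin D, times the rate of serious toxicity among them, times the share of sites that read the text literally. Only the first factor can be derived, so the product cannot be computed. The first factor does size a retrospective search under 1:1 allocation:

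- recruited by 1 May 2025: 3,800 / 2 = 1,900;
- planned total: 4,200 / 2 = 2,100.

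These are patients whose listings would be searched, not estimates of missed reports.

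**The case against.** The strongest reply is that the legend is a diagnostic sequence and not a causality rule. It tells the clinician to remove competing causes, names active vitamin D among them, and only then draws its conclusion. In that order the natural meaning is that the diagnosis waits until the other calcitriol source is gone. This is the better reading, and it stands. It does not close the gap, because a case still on both drugs at awareness is not yet attributable on that reading either.

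The second reply is that the article keeps management and reporting apart. Section {11b} lists toxicity and serious adverse reactions as separate grounds for discontinuation, and the reporting paragraph of {22} cites neither figure. This also stands, and it limits what may be claimed. A reader might infer that sites have used the legend as a reporting rule and that cases have gone unreported. The document does not support that: it reports no such use and no missed case.

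The third reply is that the flow charts and the full protocol, which may define causality for reporting, are not shown. That is a fair limit on severity. The two sentences in question are nonetheless stated in the article, so this is not an omission that a condensed article leaves elsewhere.

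The fourth reply is that the scenario is narrow. Fig. 1 gives priority to withdrawing active vitamin D, after which the legend no longer blocks attribution. What remains is the case that is already serious before withdrawal. That is a small window, but it is the one in which a 24-hour report matters.

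**Conclusion.** The point holds as a wording defect of low severity. The legend's unqualified exclusion goes further than the article's own mechanism allows. Joined to the direct-attribution trigger, it means that a serious toxicity case on both drugs need not be sent as a 24-hour report under the text as written. The consequence is delay on one route, with line listings, registry calcium and IDMC review behind it.

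A reader might go further and conclude that safety monitoring for hypercalcaemia is disabled in co-treated patients. That does not follow: the claim is confined to vitamin D toxicity, and the three later sources operate whatever the site decides.

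The conclusion assumes that sites work from the wording shown and that the full protocol sets no lower causality threshold. If it does set one, the practical effect shrinks to an inconsistency in the article. The number of affected cases cannot be computed, because the article gives neither the share of patients on active vitamin D nor a rate of serious toxicity.

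**What to change.** 1. **Fig. 2 legend.** Change the conclusion so that toxicity cannot be attributed to cholecalciferol *alone* during co-treatment. Add one sentence saying that the algorithm guides clinical work-up and dosing only and does not decide causality for safety reporting.
2. **Adverse event reporting and harms {22}.** Replace the direct-attribution test with *a reasonable possibility that cholecalciferol contributed, whatever active vitamin D is taken*. If the full protocol already uses that threshold, bring the article into line with it.
3. **One retrospective search.** Trial status gives follow-up as ending by Q4 2025, so new wording will govern few future events. Search the existing SAE line listings once, centrally, for hypercalcaemia or vitamin D toxicity in the cholecalciferol arm (about 1,900 to 2,100 patients). Assess causality for the cases found, and query only the sites concerned.

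The cost is two short wording changes and one search of listings already produced. A note to the 55 active units is optional and of limited value this late. The downside is a few extra reports and site queries.
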